### Sample size

Sample size was estimated in the WinPepi 11.1 software suite, using readmission or emergency department visit within 90 days of randomization as the endpoint [16]. Considering a 20% relative reduction in readmissions or emergency department visits in the intervention group, a significance level of 0.05, a statistical power of 80%, and an attrition rate of 20%, the sample size was set at 270 patients (135 in each group).

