At 90 days, the study endpoint (readmission or emergency department visit, change in CCS, deterioration in NYHA functional class, and HF-related mortality) shall be assessed by means of a chart review, consisting of an analysis of patients’ records. Patients who sought care at an outside facility shall be asked to provide their progress notes or discharge summary. Chart-based endpoints are expected to be confirmed by telephone contact with participants in both groups (Figure 1).

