### Endpoints

The endpoints include hospital readmission and/or emergency department visits due to HF decompensation within 90 days, two-point change in CCS, and deterioration of NYHA functional class. The secondary outcome shall be a composite of the aforementioned primary endpoints and 90-day HF-related mortality.

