### Statistical analysis

Continuous variables shall be expressed as means and standard deviations if normally distributed or medians and quartiles otherwise. Categorical variables shall be expressed as absolute and relative frequencies. Depending on the distribution of variables, baseline characteristics and the effect of the trial intervention shall be compared by means of Student’s *t-*test or the Mann-Whitney *U* test (for continuous variables) or Pearson’s chi-square test (for categorical variables). A *P* value <0.05 (two-tailed) shall be considered statistically significant. Intention-to-treat analysis shall be employed for all patients who meet a trial endpoint before 90 days. All statistical analyses shall be carried out in Statistical Package for the Social Sciences (SPSS) 18.0.

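### The 90-day readmission/emergency-visit endpoint is tested as a yes/no by chi-square despite 20% planned attrition, leaving event times and event-free partial follow-up unused

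*Protocol article*

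**What the plan says.** All references are to the protocol article.

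- **Endpoints** lists "hospital readmission and/or emergency department visits due to HF decompensation within 90 days" first. **Sample size** bases the calculation on the same event, "using readmission or emergency department visit within 90 days of randomization as the endpoint".
- **Sample size** gives the inputs as "Considering a 20% relative reduction in readmissions or emergency department visits in the intervention group", with "a significance level of 0.05, a statistical power of 80%, and an attrition rate of 20" per cent, leading to 270 patients, 135 per arm. It states no control-arm event rate.
- **Statistical analysis** names the tests for intervention effects: "the effect of the trial intervention shall be compared by means of Student’s *t-*test or the Mann-Whitney *U* test" for continuous variables and "Pearson’s chi-square test (for categorical variables") for the rest. It names no time-to-event method. Its one statement on the analysis set applies intention-to-treat to patients who reach an endpoint before day 90. Patients lost without an event are not mentioned.
- **Study protocol** says that the 90-day endpoint "shall be assessed by means of a chart review, consisting of an analysis of patients’ records". Outside records are requested from patients treated elsewhere, and telephone confirmation is expected in both groups. Only the intervention arm receives the four weekly calls; both arms return at 30 days.

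**The concern.** The sizing endpoint is an event with a date, counted from randomisation and found in charts and discharge summaries. A chi-square on proportions needs a known 90-day status for every patient counted. With 20% attrition, 0.20 × 135 = 27 patients per arm may lack it. Each such patient has to be dropped, called event-free, or kept only if an event came before the loss. The first option discards observed follow-up. The second misclassifies some patients. The third makes inclusion depend on the outcome, and the intention-to-treat sentence, read literally, comes close to it.

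Two things are at stake. One is efficiency: the observed days of lost patients, and the timing of events, carry information that the named test cannot use. The other is bias: if loss differs between arms, the estimated difference moves in a direction set by the coding. Differential loss is conceivable because the arms have different contact schedules.

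**Working it through.** **Step 1. The plan's own figure.** Inputs from Sample size and Statistical analysis: relative risk 0.80, two-sided 0.05, 80% power, 20% attrition, 135 per arm. That leaves 135 × 0.80 = 108 evaluable per arm. The control rate p1 is not stated, so 270 cannot be reproduced directly; p1 has to be back-solved. With p2 = 0.8·p1 and the pooled two-proportion formula

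n = [1.96·√(2·p̄·q̄) + 0.842·√(p1·q1 + p2·q2)]² / (p1 − p2)²,

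p1 = 0.827 and p2 = 0.6616 give (1.209 + 0.510)² / 0.1654² = 2.955 / 0.02736 ≈ 108. The stated inputs therefore meet 135 per arm at about 83% vs 66%. At other control rates the inflated n per arm is 1074 (30%), 485 (50%), 338 (60%) and 154 (80%).

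Other conventions also land near 135:

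- one-sided, 78% control rate: 133
- one-sided with continuity correction, 80%: 137
- inflation by × 1.2 instead of ÷ 0.8, 82%: 135
- an absolute 20-point reduction with continuity correction: 133 at 55% vs 35%, 134 at 60% vs 40%

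The 83% is thus an assumption and not a figure of the plan.

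**Step 2. Log-rank power on all 135 per arm.** Assume exponential event times and dropout reaching 20% by day 90. With time in units of 90 days, λ = −ln(1 − p) and k = −ln 0.8 = 0.223. Expected events per arm are 135·λ/(λ + k)·[1 − e^−(λ+k)], and power is Φ(√(D/4)·|ln HR| − 1.96), where D is the total number of events and HR the hazard ratio.

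- 82.7% vs 66.2%: HR = ln 0.3384 / ln 0.173 = 0.618; D = 103.2 + 81.6 ≈ 185; √46.2 × 0.482 − 1.96 = 1.32; power 90.6%. Chi-square on 108 completers has 80.0%.
- 60% vs 40%: HR = 0.511/0.916 = 0.557; D = 73.8 + 48.9 = 122.7; √30.7 × 0.584 − 1.96 = 1.28; power 89.9%. Chi-square on 108 has 84.1%.

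**Step 3. Simulation.** 6,000 to 10,000 trials per row, 135 per arm, 20% dropout at uniform times over 90 days, constant hazards. Power in %:

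| Rates | χ², completers only | χ², lost kept only with event | χ², lost = event-free | χ², 90-day status known for all | Log-rank with censoring | Gain over completers |
|---|---|---|---|---|---|---|
| 82.7 vs 66.2 | 80.6 | 82.9 | 82.1 | 89.0 | 91.1 | 10.5 |
| 60 vs 48 | 42.7 | 45.6 | 43.4 | 49.3 | 49.4 | 6.7 |
| 50 vs 40 | 31.6 | 33.9 | 34.6 | 37.6 | 35.7 | 4.1 |
| 40 vs 32 | 24.2 | 24.9 | 25.3 | 27.7 (formula) | 26.0 | 1.8 |

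Against the two other codings the gain at 50 vs 40 is 1.1 to 1.8 points, and at 40 vs 32 about 1 point. If nearly all dropout comes at the very start, the top row becomes 80.9% (completers) against 86.7% (log-rank).

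Most of the top-row gain comes from retaining dropouts. Chi-square with every 90-day status known already reaches 89%, so event timing adds about 2 points there.

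**Step 4. Bias if loss differs by arm.** Illustration only: 30% loss in control, 10% in intervention (20% on average), loss at uniform times, true risks 50% vs 40%. The mean probability of an event before loss is 1 − p/h with h = −ln(1 − p): control 1 − 0.5/0.693 = 0.279; intervention 1 − 0.4/0.511 = 0.217.

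- Lost patients coded event-free unless an event was seen: 0.7×0.5 + 0.3×0.279 = 0.434 vs 0.9×0.4 + 0.1×0.217 = 0.382. The difference is 5.2 points, against a true 10.
- Lost patients kept only with an event: 0.434/(0.7 + 0.084) = 0.553 vs 0.382/(0.9 + 0.022) = 0.414. The difference is 13.9 points.

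**The case against.** A reader might infer that the plan loses about 10 points of power on its own inputs, or falls short of its target. The article does not support either. It states no control rate, and its only background figure is about 50% readmitted within 6 months of discharge, 70% of these for worsening HF. That is a different population and omits emergency visits, but it lends no support to 83% at 90 days. The 80% also already allows for a comparison of proportions after 20% attrition. What is lost is a gain that could have been had.

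Attrition is also not the same as unknown 90-day status. The endpoint comes from charts, outside records and a telephone check in both groups, so a patient who misses the 30-day visit may still have a known outcome. This stands, and it can reduce the gain to little or nothing.

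A 90-day proportion matches the stated objective, and chi-square is a valid test of it. Log-rank also gives credit for mere delay. This too stands, and it is why the 90-day risk difference should remain a reported result.

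One could argue for a much larger gain if the effect falls wholly in the 30 days of calls: power at 50% vs 40% then rises from about 32% to 57%. But under a constant control hazard this needs a hazard ratio of about 0.21 in that month (0.27 at 40% vs 32%), far beyond the planned effect. It is an extreme case and should not be used to size the point.

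Finally, the coding of lost patients is often left to a full analysis plan, and no differential loss is reported; the 30%/10% split is assumed. That silence is not the point. The point is that the article does fix the test, and words its intention-to-treat rule by outcome.

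**Conclusion.** The point holds in a limited form. The article commits a dated 90-day endpoint to a yes/no chi-square while planning for 20% attrition, and its only analysis-set rule depends on having had an event. Event times and event-free partial follow-up are therefore not used.

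Under proportional hazards and dropout spread over the 90 days, the forgone power is:

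- up to about 10 points if the control rate is about 83% (back-solved) and dropouts are excluded
- about 5 to 6 points at 60% vs 40%
- about 1 to 4 points at control rates of 40% to 50% with a 20% relative reduction
- smaller or nil if 90-day status is recovered for nearly everyone

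The bias is conditional. It arises only if loss differs by arm and one of the two codings in Step 4 is used. Censoring removes it only when loss is non-informative.

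**What to change.** In Statistical analysis, replace the chi-square for this endpoint with the following:

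- Analyse all randomised patients, in the arm assigned, by time from randomisation to first HF readmission or emergency visit, with a log-rank test and a Cox hazard ratio.
- Report Kaplan-Meier 90-day risks by arm, their difference and its 95% CI, so that the 90-day objective is still answered directly.
- Censor at day 90 or at the last date on which event status is known from the chart review or telephone confirmation, by the same rule in both arms. Do not censor at the last trial call or visit, because those schedules differ by arm.
- Treat death as a competing event (with cumulative incidence in place of Kaplan-Meier), or include it through the composite already planned. That composite counts only HF-related deaths, so other deaths still need a rule.
- Keep the chi-square as a sensitivity analysis, with the coding of patients of unknown status written down.
- Record the date of first event and the date of last known status on the 90-day chart review.

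The cost is a few sentences and two date fields. SPSS, which the article names, has Kaplan-Meier and Cox procedures, and no extra patients or visits are needed. With 66 of 270 enrolled at the time of the article, dates for earlier patients should be recoverable from charts and discharge summaries. The change should be made before outcomes are compared by arm. One small downside is that a single hazard ratio averages over the month with calls and the two months without, which is a further reason to report the 90-day risk difference beside it.

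### The intention-to-treat sentence makes the analysis set conditional on meeting an endpoint, and nothing else in the article says that all randomised patients are analysed as allocated

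*Protocol article*

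**What the plan says.** Under Statistical analysis, the protocol article states that "Intention-to-treat analysis shall be employed for all patients who meet a trial endpoint before 90 days". No other section defines who is analysed, and none says that all randomised patients are analysed in the group to which they were allocated.

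The events that qualify a patient are those listed under Endpoints: "hospital readmission and/or emergency department visits due to HF decompensation within 90 days, two-point change in CCS, and deterioration of NYHA functional class". HF-related death is added to these in the composite secondary outcome. Categorical outcomes are compared between the groups by "Pearson’s chi-square test (for categorical variables").

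Two other places bear on the denominator. Sample size allows for "an attrition rate of 20"%. Study protocol has 90-day outcomes taken from chart review, asks patients treated elsewhere for their records, and expects confirmation by telephone in both groups.

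**The concern.** Intention to treat protects the randomised comparison because membership of the analysis set is fixed at randomisation and cannot depend on what happens later. The sentence reverses this by naming the outcome as the condition for the principle to apply.

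This is more than a detail left to a separate analysis plan. The article states a rule, and the rule is wrong as worded. An analyst could follow it, produce a comparison whose denominator depends on the outcome, and report it as intention to treat. The comparison affected is the main one, the 90-day event proportion in each group.

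**Working it through.** The article gives no figure to reproduce on this point. The planned total of 270 cannot be recalculated because no control event rate is stated, and the point does not depend on it. The event rates and losses below are assumptions, apart from the 135 patients per group and the 20% relative reduction, which come from Sample size.

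**Reading 1: literal.** Only patients who meet an endpoint are in the set.
- The any-endpoint rate is then 100% in each group and the relative risk (RR) is 1.00, whatever the true effect.
- Illustration: if 35% of controls and 28% of intervention patients (0.80 × 35%) meet an endpoint, the set holds 135 × 0.35 + 135 × 0.28 = 47.25 + 37.8, about 85 of 270 patients.
- Suppose patients are selected on any endpoint but only readmission or emergency visit is compared, and another endpoint occurs independently in a fraction q of patients. The observed rate is p / (p + (1 − p)q).
  - q = 0.20: 0.35/0.480 = 72.9% versus 0.28/0.424 = 66.0%, RR 0.91.
  - q = 0.40: 0.35/0.610 = 57.4% versus 0.28/0.568 = 49.3%, RR 0.86.
  - The true RR in both cases is 0.80.

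**Reading 2: the sentence only protects patients with events.** They stay in their allocated group, while a fraction d of event-free patients is lost and drops out of the denominator. The observed rate is p / (p + (1 − p)(1 − d)).

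No true effect, p = 0.35:

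| d among event-free patients | Loss among all patients, 0.65 × d | Observed rate |
|---|---|---|
| 0.10 | 6.5% | 0.35/0.935 = 37.4% |
| 0.20 | 13.0% | 0.35/0.870 = 40.2% |
| 0.30 | 19.5% | 0.35/0.805 = 43.5% |

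Loss of 10% in one arm and 30% in the other gives a spurious difference of about 6 points, with the higher rate in the arm that loses more. The same contrast gives 26.3% − 21.7% = 4.6 points at p = 0.20 and 58.8% − 52.6% = 6.2 points at p = 0.50. For scale, the planned 20% relative reduction is 7 points at a 35% control rate.

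True RR 0.80 (35% versus 28%):
- Equal loss, d = 0.20 in both arms: 32.7% / 40.2% = RR 0.81.
- d = 0.10 intervention, 0.30 control: 30.2% / 43.5% = RR 0.69.
- d = 0.30 intervention, 0.10 control: 35.7% / 37.4% = RR 0.95.

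**Reading 3: ordinary intention to treat, badly worded.** Patients who reach an endpoint early, and so miss later calls or the 30-day visit, still count in their arm, as does everyone else. There is then no selection on outcome and no bias from this source.

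**The case against.** The strongest reply is that the sentence does not say other patients are excluded. A chi-square comparison of proportions needs event-free patients, and the 90-day chart review with telephone confirmation covers both groups. Both presuppose that event-free patients are counted, and Reading 3 fits them. This stands. A reader might infer that the plan will analyse only patients with events, or that it keeps event-free patients only if they complete follow-up. The article states neither.

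The size is also open to attack, and most of that attack holds:
- The formula applies loss to event-free patients only. At p = 0.35, d = 0.20 is 13% of all patients, so it must not be equated with the plan's 20% attrition.
- If patients who would have had events are lost at the same rate, the factor (1 − d) cancels and the observed rate returns to p.
- Equal loss barely moves the RR.
- The article gives no ground for saying which arm would lose more. The intervention arm has weekly calls and the control arm has none.
- Trial status reports 58 of 66 enrolled patients as having completed, so at most 8/66 = 12% had not, and some of those may still have been in follow-up.
- Chart review can recover readmissions and emergency visits in patients who miss the 30-day visit. The congestion score and NYHA class are more exposed, because they need an assessment.

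None of this supplies the missing statement that all randomised patients are analysed as allocated.

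**Conclusion.** The point holds as a defect in the stated rule. The article's one sentence on the analysis population ties intention to treat to meeting an endpoint, and no other section corrects it. That conclusion needs no numerical assumption.

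Whether bias would follow depends on how the sentence is applied. Literally applied, the any-endpoint comparison carries no information. If it only protects patients with events, a spurious difference of about 5 to 6 points is possible, but this requires an assumed true rate of 20% to 50%, loss confined to event-free patients, and a 10% versus 30% split between arms. The direction is unknown. Under the charitable reading there is no bias. It would go too far to say that the trial's event rates will be distorted, or that its 20% attrition allowance implies a particular distortion.

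**What to change.** Replace the sentence with:

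*The primary analysis includes all randomised patients in the group to which they were allocated, whether or not they meet an endpoint or complete the calls or the 30-day visit.*

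Keep the stated chi-square comparison. Add a sensitivity analysis for patients whose 90-day status is unknown, for example counting them all as event-free and then all as events. The detail can sit in the analysis plan.

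The cost is one sentence and one additional analysis, with no extra patients or procedures. Trial status shows 66 of 270 patients enrolled, so the change can be documented well before the final analysis. A time-to-event analysis is optional: it would need event dates, which the article's account of the chart review does not mention, and it does not suit the congestion-score and NYHA endpoints.

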## Discussion

Patients in the intervention group (IG) and control group (CG) undergo routine assessment during physician or nurse visits by means of the CCS. This instrument tests for and scores the presence of crackles, elevated central venous pressure, jugular venous distension, third heart sound, orthopnea, hepatojugular reflux, and peripheral edema. It also assesses functional class by means of the New York Heart Association (NYHA) Functional Classification scale. Total scores range from 1 to 22. Scores ≥5 were found to be associated with congestion in a study of the clinical applicability of the AAD [14].

Data are also collected on weight, height, history of present illness, past medical history, comorbidities, echocardiographic findings, current prescriptions, sex, age, skin color, educational attainment, and household income. Laboratory parameters (serum sodium, potassium, urea, and creatinine levels) shall be recorded at randomization. If diuretic dose adjustments are required on two consecutive visits, a further battery of these tests shall be ordered.

Patients shall be instructed to return at 30 days for a face-to-face assessment visit.

## Trial status

The trial is currently in the patient recruitment stage. Thus far, 66 patients have been enrolled, 58 of whom have completed the trial.

## Abbreviations

AAD: Algoritmo de ajuste de diurético
CCS: Clinical congestion score
CG: Control group
DTA: Diuretic treatment algorithm
HCPA: Hospital de Clínicas de Porto Alegre
HF: Heart failure
IG: Intervention group
NYHA: New York heart association
PROBE: Prospective randomized open blinded endpoint
RCT: Randomized clinical trial
SPSS: Statistical package for the social sciences
U.S.: United States
